**Revision Chronology:**

| August 2021 | Original |
| --- | --- |
| March 2022 | 2^nd^ Version |
| January 2023 | 3^rd^ Version |

# Funding

This trial is fully funded by the German Innovation Fund of the Federal Joint Committee of Germany from September 2020 to February 2024 (01NVF19022). This funding source had no role in the design of this study and will not have any role during its execution, analyses, interpretation of the data, or decision to submit results

**Authors contributions**: S.W., J-M.Z., B.S., N.E-K., L.Z., L.S., A.R-M., M.H., G.S., T.E. contributed to the conception and the design of the study. Original draft preparation was done by S.W. All authors contributed to the drafting and revision of the final study protocol. S.W., J.-M.Z., B.S, J.W., L.B., A.-K.F. are responsible for study organization, recruitment and diagnostics, training of the exercise therapists and data management. S.R., D.-V.F. and G.S. are responsible for the process evaluation, development of treatment fidelity score, data management. F.H., A.R. and A.R.-M. are responsible for the app development and maintenance, S.P. is responsible for the recruitment of the study sites and the qualification of the exercise therapists, N.E.-K. and L.Z. are the representatives of the 2 health insurances, providing the routine data for the health economics analysis and support patient recruitment, E.H., K.T., T.N. and T.E. are responsible for data management, data handling, the randomization procedure, analysis of treatment fidelity and statistical analysis, S.K., S.F., L.S. are responsible for the health economics analysis. All authors have read and agreed to the published version of the manuscript.

# Introduction

*Item 6a: Description of research question and justification for undertaking the trial, including summary of relevant studies (published and unpublished) examining benefits and harms for each intervention.*

Epidemiological data from 2019 suggests that 15.6 % of the German population suffered from any mental disorder in 2019 (point prevalence) (Global Burden of Disease Collaborative Network, 2020). Mental disorders result in a considerable burden of disease, for example accounting for 6.4 % of overall disability-adjusted life years (DALYS) assessed in the 2019 epidemiological survey (Global Burden of Disease Collaborative Network, 2020). From 2008 to 2018, the proportion of mental disorders among all causes of death increased from 2.2% to 6.1% (Boehm, 2021). The most prevalent disorders in Germany are anxiety disorders and trauma- and stress-related disorders (point prevalence: 7.1 %), major depressive disorders (point prevalence: 4.3 %), as well as insomnia (point prevalence: 4 %) (Global Burden of Disease Collaborative Network, 2020; Hajak, 2001). Notably, these disorders often occur comorbidly (Kessler et al., 2005) and share common underlying aetiological and even maintenance mechanisms, such as high perceived stress (Hall et al., 2007; Kendler et al., 1999; Moreno-Peral et al., 2014), low self-efficacy (Iancu et al., 2015; Maciejewski et al., 2000), sleep disturbances (Harvey, 2002), elevated anxiety sensitivity (Coles et al., 2015; Naragon-Gainey, 2010; Olatunji & Wolitzky-Taylor, 2009), or repetitive negative thinking (Harvey, 2002; Wahl et al., 2019).

Worldwide, 27.2% of the DALYS attributable to mental disorders can be explained by major depressive disorders and 16.3 % by anxiety disorders (Rehm & Shield, 2019). In 2015, health care costs in Germany caused by mental disorders amounted to 44.4 billion euros (Destatis [Statistisches Bundesamt], 2015). Of this, 8.7 billion euros can be attributed to major depressive disorders, 1.7 billion euros to phobic and other anxiety disorders, and 1 billion euros to insomnia. Mental disorders account for 13.1% of total costs and represent the second highest cost group after cardiovascular disorders (46.4 billion euros, 13.7% of total costs). Major depressive (RR = 2.63) and anxiety disorders (RR = 1.41) have also been shown to increase the risk of cardiovascular disease (De Hert et al., 2018). Besides direct costs (e.g., treatment costs), mental disorders cause indirect costs on the German job market. With 14.4 billion euros overall, mental disorders caused the second-highest lost production costs of all diagnosis groups in 2019 (Federal Institute for Occupational Safety and Health [Bundesanstalt für Arbeitsschutz und Arbeitsmedizin (BAuA)], 2021). They further caused 117.2 million days (16.5% of all days) of incapacity to work, which is the longest absences per sick leave of all disorders (Rabe-Menssen et al., 2021). Amongst mental disorders, major depressive disorders accounted for the most days of incapacity to work (33.9 million days), followed by trauma- and stress-related disorders (21.6 million days). Anxiety disorders accounted for 7.6 million days and insomnia for 0.5 million days.

Despite the severe negative impact of mental disorders, it is estimated that in Germany only 10% of all affected individuals receive evidence-based treatment and only 2.5% receive psychological treatment (Nübling et al., 2014). In addition, even those receiving psychological treatment often have to wait before treatment initiation; for example, 40 % of outpatients waited three to nine months to start psychotherapeutic treatment in German health care settings (Federal Chamber of Psychotherapists [Bundespsychotherapeutenkammer (BPtK)], 2021). Longer waiting times are associated with worsening and chronicity of symptoms and the development of comorbid conditions ((BPtK)], 2018). The high prevalence and severe burden of mental disorders in combination with the large gap between people in need for treatment and those actually receiving it (Patel, 2012) illustrates the need to develop alternative efficacious, effective and efficient treatments.

Exercise, defined as physical activity that is planned, structured and repeated, with the primary aim to improve or maintain physical fitness (Caspersen et al., 1985, p. 128), has revealed positive therapeutic effects for diverse mental disorders (Ashdown-Franks et al., 2020). Most of the studied exercise interventions include aerobic activities (i.e. running) or a combination of aerobic exercise with strengthening activities. Recent meta-analyses on major depressive disorders and insomnia have shown large effects for exercise that were comparable to those of psychological treatment and psychopharmacological treatment (Banno et al., 2018; Morres et al., 2018). A recent meta-analysis on PTSD (Rosenbaum et al., 2015) found small to moderate effects; however, in two of the four studies included, the intervention comprised yoga. Looking at more recent evidence from RCTs focusing on interventions including aerobic exercise, large treatment effects were found (Goldstein et al., 2018; Powers et al., 2015). For panic disorder (with and without agoraphobia), RCTs have revealed large effects on symptomatology with both, acute exercise and structured multi-week aerobic exercise programs (Broocks et al., 1998; Esquivel et al., 2008). In addition, moderate to large effects have been reported for exercise as an augmentation to TAU for major depressive disorders, panic disorder and PTSD (Gaudlitz et al., 2015; Legrand & Neff, 2016; Powers et al., 2015). Key components of exercise interventions that have shown optimal therapeutic efficacy among patients with major depressive disorders, insomnia, panic disorder with or without agoraphobia and PTSD (Aylett et al., 2018; Jacquart et al., 2019; Morres et al., 2018; Stubbs et al., 2018) include aerobic exercise at a minimum of moderate intensity (MVAE) either or a combination of MVAE with resistance training, conducted two to three times per week, for 10 weeks with a session duration of at least 30 minutes, partially supervised or non-supervised.

Exercise might not only be a promising efficacious treatment but also carry the advantage of being highly efficient, since it can be delivered in group settings with relatively short durations (Morres et al., 2018), can be offered to patients with heterogeneous and burdensome mental disorders, can be expected to show a low likelihood of adverse effects, comes at a relatively low cost, and is suited to reduce the risk for cardiovascular diseases that frequently occur comorbid with mental disorders (Fiuza-Luces et al., 2013; Naci & Ioannidis, 2015). Furthermore, exercise can be performed and continued independently without professional supervision or only remote supervision. However, individuals suffering from mental disorders often have difficulties to initiate and maintain a physically active lifestyle (Schuch et al., 2017), which may be related in part to deficiencies in motivation and exercise-related self-regulatory skills in this population (Kramer et al., 2014). Reassuringly, there is evidence showing that exercise adoption and maintenance are mediated by motivational and volitional aspects, such as intention strength, action planning and barrier management (Fuchs et al., 2012). A recent meta-analysis shows that especially self-efficacy in building intentions and action planning is crucial for sustained exercise behavior change (Zhang et al., 2019). One possible way to promote such motivational and volitional aspects are the application of behavior change techniques (BCTs) (Abraham et al., 2009; Michie et al., 2011).

The combination of behavior change techniques and exercise as a structured intervention appears highly promising in terms of initiating a sustainable exercise behavior change. Since outpatients have less supervision and contact to their therapists compared to patients in inpatient or rehabilitative mental health care settings, structured exercise interventions in combination with behavior change techniques to overcome general and disorder-specific barriers might be especially important within the outpatient mental health care setting. Indeed solely exercise on prescription (or on referral) for outpatients shows drop-out rates of nearly 80% (Crone et al., 2008), whereas structured exercise interventions in combination with BCTs for outpatients show lower dropout rates and stronger effects on mental health (Morres, et al., 2019).

Therefore, ImPuls was developed and evaluated as a complex exercise program with respect to the Medical Research Council (MRC) framework, specifically designed to scrutinize an additional treatment option in the outpatient mental health care system in Germany (Wolf et al., 2020). It has been successfully evaluated in terms of efficacy and acceptability in a feasibility study for outpatients waiting for psychotherapeutic treatment (Zeibig et al., 2023; Zeibig et al., 2021). A broader and more comprehensive pragmatic trial was needed to explore the extent to which the intervention also achieves its effect in a real-world setting (e.g., with exercise therapists working in the outpatient setting as intervention deliverers alongside their daily business; as an add-on to treatment as usual; with a realistic referral system) (Ford & Norrie, 2016). Therefore, it is now conducted in a pragmatic multi-site randomized controlled trial to investigate efficacy and cost-effectiveness within the real-world outpatient setting (Wolf et al., 2021).

The complexity of ImPuls (i.e., several interacting factors [e.g., BCTs and Exercise], involvement of different actors [exercise therapists, managers of outpatient rehabilitative and medical care facilities, patients] etc.) and the future need to implement the intervention into a comprehensive health service provision prompts the necessity of research beyond a pure evaluation of efficacy, namely process evaluation. Thus, the ImPuls study is accompanied by a comprehensive process evaluation based on the MRC framework (Moore et al., 2015) and its complement (Skivington et al., 2021), the former of which provides comprehensive and detailed guidance (Fynn et al., 2020). Using a mixed-methods approach may be particularly helpful to understand multiple perspectives, multiple types of causal processes and multiple types of outcomes which in turn are common aspects of implementation research (Peters et al., 2013).

Process evaluation in studies evaluating exercise interventions has been slowly emerging during the last decade (Ellard et al., 2014; van Dongen et al., 2018; Voorn et al., 2016). However, process evaluation of exercise interventions offered to patients with mental disorders is rarely conducted. For example, a recent and very reputable meta-analysis on the effects of exercise on depression included 11 studies (Morres, et al., 2019). None of the included studies integrated a process evaluation. If process evaluations are conducted within this field, they are sparse and often limited. For example, one study with adolescents focused solely on selected aspects like adherence rate of the participants, acceptability and feasibility (Jarbin et al., 2021), which means that only specific subcomponents of the MRC framework were taken into account. Other studies exclusively conducted qualitative interviews (Carr et al., 2021; Walburg et al., 2022), which ideally should be complemented by quantitative methods to provide an encompassing insight into the processes relevant for implementation (Peters et al., 2013). Another study heeds the aforementioned deficiencies, yet apparently seems to omit investigation of interactions (e.g., between participants and the intervention / - deliverers) with regard to the MRC framework key component mechanisms of impact (Farrand et al., 2014). Given the lack of comprehensive process evaluations accompanying exercise programs for patients with heterogeneous mental disorders, the respective evidence for implementation conditions is weak. Consequentially, further research in this area is needed.

*Item 6b: Explanation for choice of comparators.*

The TAU condition will be modelled to represent the typical treatment patients receive in the German outpatient health care system. Therefore, patients will not be actively provided with any treatment but patients are allowed to receive any intervention that is available to them. Any evidence-based treatment provided by the outpatient mental health care system will be recorded, i.e., any psychiatric/pharmacological or psychological/psychotherapeutic intervention. Interventions, delivery or dosage of the intervention can be changed and adapted during the course of the study.

*Item 7: Specific objectives or hypotheses.*

Despite the promising evidence for MVAE as an intervention for patients with mental disorders, exercise programs or professional exercise therapy are currently not provided as regular health services within the outpatient mental health care system in Germany. With the aim of combining the current evidence on the efficacy of MVAE and sustained exercise behavior change with specific demands of a real-world outpatient health care setting, ImPuls was developed as a manualized group exercise intervention (Wolf et al., 2020; Zeibig et al., 2021) for physically inactive outpatients suffering from major depressive disorders, insomnia, panic disorder with or without agoraphobia and PTSD. ImPuls integrates recent findings about the optimal modalities of exercise for therapeutic efficacy, such as optimal frequency, intensity, time/duration and type of exercise (FITT criteria) for the targeted disorders and evidence regarding sustainable behavior change by integrating behavior change techniques (BCTs). The components of this intervention are further tailored towards the specific needs of outpatients with mental disorders in the current German mental health care setting. Specific features are 1) the inclusion of a broad range of heterogenous diagnoses for which prior research has demonstrated therapeutic efficacy, 2) intervention delivery in group format, and 3) short duration (i.e., only 4 weeks of supervised MVAE sessions carried out inhouse in each study site). The aim of the current study is to investigate the efficacy and cost-effectiveness of implementing ImPuls within the outpatient mental health care setting in Baden-Württemberg, a representative state in South-West Germany. The following hypotheses will be tested:

1. Participants in the intervention condition, who have received ImPuls in addition to TAU, will show lower global symptom severity at post-treatment and follow-up assessments compared to a control condition with TAU only.

2. Overall costs in the intervention condition will represent a significant saving for the public health system compared to the control condition at post-treatment and follow-up assessments.

3a. The intervention will lead to significantly higher levels of MVAE at post-treatment and follow-up assessments compared to the control condition.

3b. The effect of condition on the reduction of the primary outcome global symptom severity will be mediated by an increase in MVAE.

4. Participants in the intervention condition will show lower disorder-specific symptoms (major depressive disorder, insomnia, panic disorder with or without agoraphobia and PTSD) compared to participants in the control condition at post-treatment and follow-up assessments

We will further assess, if participants in the intervention condition show more instances of clinically significant change compared to participants in the control condition at post-treatment and follow-up assessments (Additional analysis to Hypothesis 1 and 4)

The main objectives of our process evaluation are a) to support the findings of the ongoing pragmatic randomized controlled trial by confirming that its efficacy is truly attributable to the ImPuls intervention and b) to discover further crucial factors for the implementation of ImPuls into real-world outpatient mental health care settings.

The main research questions of the process evaluation are:

1. Implementation:
   1. To what extent did our actions empower exercise therapists (i.e., competence, acceptance) to deliver the intervention?
   2. To what extent do exercise therapists implement intervention components as intended (treatment fidelity) and what are reasons for its potential variance?
   3. Which strategies recruited the most patients and how valid were the referrals in terms of acquisition/inclusion?
   4. How do referring healthcare professionals rate the ImPuls intervention in terms of acceptability, appropriateness and feasibility?
   5. To what extent were all ImPuls sessions offered as planned and all telephone contacts made as scheduled?
2. Context:
   1. What barriers and facilitators did exercise therapists and managers experience concerning the implementation of the ImPuls intervention?
3. Mechanisms of Impact:
   1. To what extent do attitudes of exercise therapists towards the ImPuls intervention (e.g., acceptability, appropriateness) moderate the treatment effects?
   2. To what extent do patients’ integration of core components of the ImPuls intervention (e.g., amount of exercise, barrier management, goal-setting) as well as changes in respective individual behavioral determinants (e.g., action and coping plans; physical activity-related health competencies) mediate the treatment effects?
   3. To what extent do patients’ integration of motivational/volitional core components of the ImPuls intervention (e.g., barrier management, goal-setting, phone contacts) as well as changes in respective individual behavioral determinants (e.g., action and coping plans; physical activity-related health competencies) mediate its effect on their exercise adherence?
   4. To what extent do changes in patients' transdiagnostic psychological processes (e.g., emotional regulation, repetitive negative thinking or perceived stress) mediate the treatment effects?

*Item 8: Description of trial design including type of trial (e.g., parallel group, crossover, factorial, single group), allocation ratio, and framework (e.g., superiority, equivalence, non-inferiority, exploratory).*

The study will be led by researchers based at the University of Tuebingen in Germany, and will be conducted in 10 different study sites across Baden-Württemberg, a region in South-West Germany. The entire project will be conducted between September 2020 and February 2024. The study has been registered at the German Clinical Trial Register (ID: DRKS00024152, 05/02/2021) and has been approved by the local ethics committee for medical research at the University of Tuebingen (ID: 888/2020B01, 02/11/2020). A pragmatic multi-site block-randomized controlled trial with two treatment arms (ImPuls + TAU vs. TAU) and three points of assessment (pre, post, follow-up) will be conducted (see fig. 1). All outcomes will be included at all assessments. Study completion and reporting will be carried out in accordance with the Consolidated Standards of Reporting Trials (CONSORT) [52], the Template for Intervention Description and Replication (TIDieR) (Hoffmann et al., 2016) and the Consensus on Exercise Reporting Template (CERT) (Slade et al., 2016).

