## Sample Size

*Item 14: Estimated number of participants needed to achieve study objectives and how it was determined, including clinical and statistical assumptions supporting any sample size calculations.*

The sample size was determined a priori using power analysis (G*Power, version 3.1.9.2) (Faul et al., 2009; Faul et al., 2007). Power analysis was conservatively based on the lowest symptom-related post-treatment effect of exercise (vs. TAU/waiting list) on all included clinical disorders, namely the effect size of d = -0.348 (g = - 0.347) for symptoms of post-traumatic stress disorder (Rosenbaum et al., 2015). A two-sided *t*-test, alpha level of 0.05, a test power of 80%, an equal cell population, and a dropout rate of 30% were assumed. This calculation resulted in N = 375, which is conservative enough to detect the lowest expected treatment effect at the post-treatment phase. However, we regarded this sample size as the minimum and targeted a total sample of N = 600, in order to have enough statistical power for further analysis performed in the course if the process evaluation (see Statistical Methods – Items 20 a, b and c). ~~that will be predefined and published in a separate study protocol regarding the evaluation of the entire implementation process based on the Medical Research Council framework.~~

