## Statistical Methods

*Item 20a: Statistical methods for analyzing primary and secondary outcomes. Reference to where other details of the statistical analysis plan can be found, if not in the protocol.*

*Item 20b: Methods for any additional analyses (e.g., subgroup and adjusted analyses).*

*Item 20c: Definition of analysis population relating to protocol non-adherence (e.g., as randomised analysis), and any statistical methods to handle missing data (e.g., multiple imputation).*

To test Hypotheses 1, 2, 3a and 4 we will use multilevel modeling to establish the treatment effects on the primary outcome (global symptom severity) and the secondary outcomes (major depressive disorders, insomnia, panic disorder, agoraphobia, PTSD, QALYs, exercise). In these analyses, each outcome will be predicted by the group (ImPuls + TAU vs. TAU), time (pre vs. post vs. follow-up), and their interaction. Given that the randomization is stratified by study site, we will account for the effects of study site in all analyses. All analyses will be performed on intention-to-treatment basis, using maximum likelihood estimations.

To test Hypothesis 3b, mediation analyses will be performed to test the indirect effects of the treatment on the primary outcome that are mediated by the changes in the putative mediators (self-reported exercise in minutes per week, accelerometry-based moderate to vigorous physical activity (MVPA); from pre to post, pre to follow-up and post to follow-up). We will compute standardized change scores for the outcome and mediators (Lee et al., 2019). In a path model (specified in the framework of structural equation modeling), the group variable predicts the changes in the mediators, and these mediating factors further predict the change score in the outcome. The indirect effects are defined by the products of the group-mediator and mediator-outcome effects. As exploratory analyses, we will also examine other forms of mediations proposed by Goldsmith et al. (Goldsmith et al., 2018), encompassing cross-lagged effects and latent change score models. As recommended by Usami et al.(Usami et al., 2019), we will first test whether these models fit the data well (and which model fits the data best), and then investigate the indirect effects of the treatment on the outcome.

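### The stated model leaves the arms free to differ at a baseline measured before randomisation, which gives away precision, and Hypothesis 1 covers two time points while the sample size covers one

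*Protocol*

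**What the plan says.** The protocol fixes three things that bear on the primary comparison.

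- **Hypothesis 1** (Introduction, Item 7): patients given ImPuls plus TAU "will show lower global symptom severity at post-treatment and follow-up assessments compared to a control condition with TAU only". The Primary Outcome section defines the BSI-18 Global Severity Index and names no primary time point.
- **Model** (Statistical Methods, Items 20a-c): "each outcome will be predicted by the group (ImPuls + TAU vs. TAU), time (pre vs. post vs. follow-up), and their interaction". Study site is accounted for and estimation is by maximum likelihood. Pre is one of the outcome time points, and nothing constrains the arms to be equal there.
- **Sample size** (Item 14): one comparison, described as "A two-sided *t*-test, alpha level of 0.05", with 80% power, equal arms and 30% dropout. The effect is "namely the effect size of d = -0.348 (g = - 0.347) for symptoms of post-traumatic stress disorder". The resulting N = 375 is called "conservative enough to detect the lowest expected treatment effect at the post-treatment phase". It is treated as a minimum. The target is N = 600, and the extra patients are justified by the process evaluation.

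On timing, Recruitment (Item 15) places the pre-assessment in a 14-day window with randomisation on Day 15, and the note to Table 5 also puts the patients' pre-assessment before randomisation. Post and follow-up are 6 and 12 months after randomisation.

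**The concern.** Because pre precedes randomisation, the two arms share one expected pre mean. A model with group, three-level time and their interaction estimates a separate pre mean for each arm and so does not use that fact. If the interaction term for post is the test, its variance carries the full noise of the observed pre difference. If the difference at post is the test, the model gains nothing from the pre score when data are complete. Either way, information the trial already collects is not turned into precision, for the primary scale or the secondary ones.

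The second issue is alignment. The hypothesis names two time points and the sizing covers one. The stated error rate and power belong to a single t-test at post. What they become for Hypothesis 1 depends on whether both time points must succeed, either suffices, or one is primary, and the protocol does not say which.

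**Working it through.** **Inputs.** From Sample Size: two-sided alpha 0.05, power 80%, d = 0.348, equal arms, 30% dropout, minimum N = 375, target N = 600. Not in the protocol and therefore assumed: pre-post correlation ρ of 0.3 to 0.6; correlation r of 0.5 to 0.8 between the post and follow-up contrasts; equal SD at each time; complete data; independent patients.

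**Step 1: reproduce the sample size.** A two-sample t-test (noncentral t) with d = 0.348 needs 131 per arm, 262 in total. 262 / 0.70 = 374.3, rounded up to 375. This matches. For the target, 600 × 0.70 / 2 = 210 per arm, and the same t-test then has 94.5% power.

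**Step 2: variance of the treatment contrast**, as a multiple v of 2σ²/n with n per arm:

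- difference in change from pre: v = 2(1 − ρ)
- difference at post, no use of pre: v = 1
- common pre mean, or pre as covariate: v = 1 − ρ²

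The third divided by the first is (1 − ρ²) / [2(1 − ρ)] = (1 + ρ)/2, which is at most 1. At ρ = 0.5 it is 0.75, a 25% smaller variance. The third divided by the second is 1 − ρ², also at most 1.

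**Step 3: power** = Φ(d√(n/2)/√v − 1.96). Here d√(n/2) is 0.348 × √65.5 = 2.816 at 131 per arm and 0.348 × √105 = 3.566 at 210 per arm. For example, at 131 per arm and ρ = 0.3:

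- change contrast: 2.816/√1.4 = 2.380, and Φ(0.420) = 66%
- constrained baseline: 2.816/√0.91 = 2.952, and Φ(0.992) = 84%

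| ρ | Change, 131/arm | Constrained, 131/arm | Change, 210/arm | Constrained, 210/arm |
|---|---|---|---|---|
| 0.3 | 66% | 84% | 85% | 96% |
| 0.4 | 73% | 87% | 90% | 97% |
| 0.5 | 80% | 90% | 95% | 98% |
| 0.6 | 88% | 94% | 98% | 99% |

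The post-level difference without adjustment stays at about 80% (131 per arm) and 94.5% (210 per arm) for every ρ.

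**Step 4: two time points.** Bivariate normal test statistics, each judged at |z| > 1.96, each time point taken as the unadjusted post-level test of Step 1:

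- Both required, equal effects: 69% (r = 0.5) to 73% (r = 0.8) at N = 375, and about 91-92% at N = 600.
- Both required, follow-up effect 75% of d (assumed): 74-76% at N = 600. At r = 0.6 and N = 375 it is 52%.
- Either suffices: familywise error is 9.1%, 8.3% and 7.8% at r = 0.5, 0.7 and 0.8.

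**The case against.** Several points count on the other side.

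- **The model is valid.** A group-by-time model fitted by maximum likelihood is standard and unbiased under randomisation. Leaving pre unconstrained is a loss of efficiency, not an error. This stands, but a more precise alternative that needs no extra data is still worth adopting.
- **The change contrast is not stated.** Hypothesis 1 speaks of lower severity at each time point, which can be read as a difference in levels. That is fair, and for that reading the 66% and 73% figures do not apply. The constrained baseline is still at least as precise, because 1 − ρ² cannot exceed 1. Nor does the change contrast always lose against the sizing t-test: it matches it at ρ = 0.5 and beats it above.
- **N = 600 is the plan.** The Recruitment section's 60 patients per site at 10 sites gives the same total. The added patients serve Hypothesis 1 whatever the reason for adding them, so the N = 375 figures describe the stated minimum and not the intended trial.
- **Testing order and multiplicity may be in the SAP**, which is not at hand. Their absence from the protocol is therefore not a finding.

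A reader might infer that neither the 5% error rate nor the 80% power holds for Hypothesis 1. The documents do not support that. The hypothesis joins the time points with a literal *and*. If both are required, error stays at or below 5% and only power falls. An either-suffices rule is nowhere stated, and it would raise power while inflating error. A joint interaction test would keep 5%. No multiplicity reading on its own breaks both figures.

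**Conclusion.** The baseline point holds. For either reading of the effect, a common pre mean or adjustment for pre is at least as precise as the stated model. The gain over the change contrast is 6 to 18 percentage points of power at the minimum N and 1 to 11 points at the target, for ρ between 0.6 and 0.3. Against an unadjusted difference at post, the gain is about 4 to 14 points at the minimum and roughly 2 to 5 at the target.

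The mismatch between a two-time-point hypothesis and a one-time-point sample size is also real, but it supports only aligning the wording. It does not show that the trial as planned is underpowered: at N = 600 with equal effects, requiring both time points still gives about 91-92%. Power falls short there if the effect wanes, for example 74-76% if three quarters of it remains at follow-up.

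All correlations and the waning are assumptions. Clustering within the randomised groups of six is ignored, so the percentages compare the options and are not planning values.

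**What to change.** In Statistical Methods, specify the repeated-measures model with one pre mean common to both arms (no group effect at pre), or use the pre score as covariate, for the primary and secondary scales.

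In Hypothesis 1 and Sample Size, do one of two things:

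- name the ImPuls-minus-TAU difference in the Global Severity Index at post (6 months) as the primary contrast at two-sided 5%, with follow-up tested confirmatorily only if post is significant; or
- state that both time points are required and restate the power for that rule at N = 375 and N = 600.

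The first option matches the existing calculation and holds the error at 5% across the two time points. If the SAP already contains a testing order, the protocol should agree with it.

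The cost is wording only, with no added patients or assessments. The small downside of the first option is that a follow-up claim depends on the post result.
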